### **7.6.2.2. Reporting Other Special Situations**

All other special situation reports must be reported on the special situations report form and forwarded to TLC within 24 hours of the investigator becoming aware of the situation to the TLC Safety email address. These reports must consist of situations that involve study drug.

Special situations involving concomitant medications do not need to be reported on the special situations report form; however, for special situations that result in AEs due to concomitant medication, the AE should be reported on the AE form.

Any inappropriate use of concomitant medications prohibited by this protocol should not be reported as “misuse” but may be more appropriately documented as a protocol deviation.

Refer to Section [7.3](#) and the CRF/eCRF completion guidelines for full instructions on the mechanism of special situations reporting.

All clinical sequelae in relation to these special situation reports will be reported as AEs or SAEs at the same time using the AE CRF/eCRF and/or the SAE report form. Details of the symptoms and signs, clinical management, and outcome will be reported, when available.

## 8. STATISTICAL CONSIDERATIONS

### 8.1. Analysis Objectives and Endpoints

#### 8.1.1. Analysis Objectives

The primary objectives of this study are as follows:

- To evaluate the safety and tolerability of escalating single and multiple oral doses of TLC-2716
- To characterize the single- and multiple-dose pharmacokinetics (PK) of TLC-2716 and its metabolite(s)

The exploratory objectives of this study are as follows:

- To evaluate the pharmacodynamics (PD) of liver X receptor (LXR) inverse agonism by TLC-2716 as measured by metabolic parameters including fasting lipids and serum biomarkers of *de novo* lipogenesis (DNL)
- To characterize TLC-2716 dose and/or exposure-response relationships for PD markers
- To evaluate exploratory biomarkers

#### 8.1.2. Primary Endpoint(s)

The primary endpoints of this study are as follows:

- PK parameters including  $AUC_{last}$ ,  $AUC_{inf}$  [single-dose],  $\%AUC_{exp}$  [single dose],  $CL/F$  [single dose],  $AUC_{tau}$  [multiple-dose],  $C_{tau}$  [multiple-dose],  $CL_{ss}/F$  [multiple dose], and  $V_z/F$ ,  $C_{max}$ ,  $T_{max}$ ,  $C_{last}$ ,  $T_{last}$ ,  $\lambda_z$ ,  $CL/F$ , and  $t_{1/2}$  of TLC-2716 and its metabolite(s), as applicable
- Incidence of AEs
- Incidence of laboratory abnormalities
- 12-lead ECG measurements and abnormalities
- Vital sign measurements
- Physical examinations

### **8.1.3. Exploratory Endpoint(s)**

The exploratory endpoints of this study include:

- PD biomarkers of TLC-2716 and its metabolites, including fasting lipids, serum ANGPTL3, ApoC3, whole blood gene expression of ABCA1 and ABCG1, biomarkers of DNL, and other exploratory biomarkers, as applicable
- Dose and/or exposure-response relationships between PK parameters and PD biomarkers of TLC-2716 and its metabolites, as applicable

## **8.2. Planned Analyses**

### **8.2.1. Dose Escalation Analysis**

For the purpose of making the decision to escalate to the next dose level/cohort, review of all available safety, tolerability, and relevant PK and/or PD data will be conducted after all subjects in each cohort have completed dosing and the necessary follow-up period has been completed, as outlined in [Section 3.2](#). For investigators, safety assessments and relevant PD data will be displayed by cohort (blinded to treatment) to facilitate the decision to dose escalate while preserving the blind at the subject level. The sponsor may separately evaluate unblinded safety, PK, and/or PD data at the cohort and subject level as necessary to support decisions regarding dose escalation and/or design and initiation of adaptive cohorts in Part C.

### **8.2.2. Final Analysis**

The final analysis will be performed after all subjects have completed the study, outstanding data queries have been resolved or adjudicated as unresolvable, and the data have been cleaned and finalized.

## **8.3. Analysis Conventions**

### **8.3.1. Analysis Sets**

#### **8.3.1.1. Safety**

The Safety Analysis Set will include all randomized subjects who received at least 1 dose of study drug. Subjects who received treatment other than that to which they were assigned will be analyzed according to the treatment received.

#### **8.3.1.2. Pharmacokinetics**

The PK Analysis Set will include all randomized subjects who received at least 1 dose of TLC-2716 and had at least 1 non-missing PK concentration value reported by the PK laboratory for each respective analyte.

### 8.3.1.3. Pharmacodynamics

Each PD Analysis Set will include all randomized subjects who received at least 1 dose of TLC-2716 and had the necessary baseline and on-study measurements to provide interpretable results for each respective PD parameter.

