### **8.8. Pharmacodynamics Analysis**

PD biomarker data, including but not limited to serum ANGPTL3, ApoC3, and markers of DNL (e.g., malonate carnitine index), if applicable, will be listed and summarized using descriptive statistics by cohort and treatment groups at individual sampling time points. Summary statistics may also be provided to characterize the effect of concomitant food intake on the PD biomarkers. Exploratory analyses may be performed to evaluate associations amongst the biomarkers and between the biomarkers and laboratory parameters.

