## **2. ANALYSIS POPULATIONS**

The analysis populations in this study are defined as follows.

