### **3. STATISTICAL CONSIDERATIONS FOR DATA ANALYSES AND HANDLINGS**

#### **3.1. Statistical Reporting**

In principle, analyses for safety will be summarized by the actual treatment group and analyses will be performed by subjects dosed with placebo and subjects dosed with TLC-2716 by cohorts for Part A and Part B. Subjects dosed with placebo will be analyzed as 1 group in each part. To assess the effect of food, analyses may be performed by fasting state and after a meal, as applicable.

Unless otherwise stated, continuous variables will be summarized by the number of non-missing observations, arithmetic mean, standard deviation (SD), median, Q1, Q3, minimum, and maximum values as summary statistics; categorical variables will be summarized by the frequency count and the percentage of subjects in each category.

All analyses will be performed using SAS Version 9.4 (SAS Institute, Cary, NC, USA).

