## **6. EFFICACY ANALYSES**

All efficacy analyses are exploratory. In MAD cohorts in Part B and C, exploratory analyses will be performed to describe absolute and relative (%) changes from baseline in lipid parameters, including fasting triglycerides, total cholesterol, low-density lipoprotein cholesterol (LDL-C), and high-density lipoprotein cholesterol (HDL-C). Exploratory subgroup analyses may also be conducted to describe changes in fasting triglycerides in subjects with baseline triglycerides  $\geq 100$  mg/dL versus  $< 100$  mg/dL. Similarly, exploratory subgroup analyses may be performed to describe changes from baseline in fasting LDL-C in subjects with baseline LDL-C  $\geq 100$  mg/dL versus  $< 100$  mg/dL.

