## **9. PHARMACODYNAMIC ANALYSIS**

Exploratory descriptive analysis of PD markers collected in this study, including absolute and relative (percent) changes from baseline, may be evaluated.

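### Protocol 8.3.1.3 defines the PD Analysis Set so that, read literally, it excludes every placebo subject; the SAP does not correct this and plans no placebo-adjusted PD estimate

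*Combined protocol and SAP*

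**What the plan says.** Protocol 8.3.1.3: "Each PD Analysis Set will include all randomized subjects who received at least 1 dose of TLC-2716", provided the necessary baseline and on-study measurements exist. The safety set in 8.3.1.1 is worded differently: "The Safety Analysis Set will include all randomized subjects who received at least 1 dose of study drug".

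Protocol 8.8 says PD biomarkers "will be listed and summarized using descriptive statistics by cohort and treatment groups at individual sampling time points". Protocol 1.3.1 explains that all MAD subjects take placebo on Day -1 so that this day can be compared with later changes on TLC-2716 or PTM.

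SAP Section 2 opens with "The analysis populations in this study are defined as follows" and lists three sets: All Randomized, Safety and Pharmacokinetic. There is no PD set. SAP Section 9 is one sentence: "Exploratory descriptive analysis of PD markers collected in this study, including absolute and relative (percent) changes from baseline, may be evaluated". SAP Section 6 says that in MAD cohorts "exploratory analyses will be performed to describe absolute and relative (%) changes from baseline in lipid parameters". Neither names an analysis set, a grouping or a comparison with placebo.

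SAP 3.1 says: "Subjects dosed with placebo will be analyzed as 1 group in each part". The sentence before it concerns safety and names only Parts A and B.

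**The concern.** Placebo subjects receive only PTM, so none meets the condition in 8.3.1.3. The phrase matches the PK set in 8.3.1.2, where excluding placebo is sensible. In a PD set it removes the randomised control.

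Without that control, two things can look like a drug effect:

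- **MAD cohorts.** Subjects are confined from Day -2 to Day 17 and dosed with standardised meals. A marker may drift over that time for reasons unrelated to drug, and one pre-treatment day cannot show this.
- **SAD cohorts.** PD consists of one pre-dose and one 4-hour sample in fed subjects (fasted dosing is possible only in Part C), with no Day -1 PD profile. For a marker outside the laboratory panel, a change at 4 hours mixes meal and drug.

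The first exploratory objective is the effect on lipids and DNL markers, and protocol 1.3 says the results, PD included, will support Phase 2 dose selection.

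**Working it through.** **1. The plan's own figures.** Protocol 8.10 gives 100 to 150 subjects at 8 active and 2 placebo per cohort. 10 cohorts x 10 = 100 and 15 x 10 = 150, so the figures reproduce. Placebo subjects: 5 x 2 = 10 per part, 10 x 2 = 20 in Parts A and B, 15 x 2 = 30 at most. Read literally, 8.3.1.3 excludes all of them.

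**2. The sections side by side.**

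| Section | Does placebo enter? |
|---|---|
| Protocol 8.3.1.3 | No: a dose of TLC-2716 is required |
| Protocol 8.8 | Yes: PD summarised by treatment group |
| Protocol 1.3.1 | Yes: changes on TLC-2716 or PTM are compared with Day -1 |
| SAP 2 | Silent: no PD set |
| SAP 6 and 9 | Silent: change from baseline only |
| SAP 7.2 and 7.2.1 | Yes, for laboratory tests: Safety set, by treatment group, with change from predose |

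The first row cannot stand with the next two. The last row covers the lipid panel in protocol 6.7.5.1 (total cholesterol, HDL-C, LDL-C, TG). It does not cover ANGPTL3, ApoC3, DNL markers or ABCA1/ABCG1, which protocol 8.1.3 lists as exploratory endpoints. For these, 8.3.1.3 is the only set definition in either document.

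**3. Precision of a placebo comparison.** Half-width = t x SD x sqrt(1/n1 + 1/n2), where SD is that of the log change. The documents give no SD; 0.2 to 0.4 is assumed.

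- One dose against its own 2 placebo subjects: sqrt(1/8 + 1/2) = 0.791; t on 8 df = 2.306; 1.82 SD, or 0.36 to 0.73.
- One dose against the 10 pooled Part B placebo subjects, simple two-sample: sqrt(1/8 + 1/10) = 0.474; t on 16 df = 2.120; 1.01 SD, or 0.20 to 0.40.
- The same contrast from one model over all 50 Part B subjects (six groups, one baseline covariate): df = 50 - 6 - 1 = 43; t = 2.017; 0.96 SD, or 0.19 to 0.38. This ignores any baseline imbalance and any gain from the covariate.
- Uncontrolled mean change in 8 active subjects: t on 7 df = 2.365; 2.365/sqrt(8) = 0.84 SD.

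Pooling makes the controlled interval only modestly wider than the uncontrolled one.

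**4. What drift could do.** Suppose there is no drug effect and a mean drift of b SD. The chance that the uncontrolled 95% CI for 8 subjects excludes zero comes from a noncentral t with 7 df and noncentrality b x sqrt(8). For b = 0.25, 0.5 and 1.0 it is about 9%, 23% and 68%. These drifts are illustrations; the documents give none.

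**The case against.** The strongest reply is that this is a slip in one definition, not a plan to discard controls. Protocol 8.8 and 1.3.1 both point to use of placebo PD data, and the SAP does not repeat the TLC-2716-only condition. That is fair. A reader might infer that the Part B control definitely falls from 10 subjects to 0. The documents support this only if 8.3.1.3 is applied literally over the sections that contradict it.

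A reader might also infer that the lipid results have no placebo control. They do not support that either. SAP 7.2 and 7.2.1 put placebo lipid changes in the tables beside active ones.

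Nor can one say that only placebo separates meal from drug throughout. MAD subjects have a Day -1 placebo-day PD profile timed to within 5 minutes of the dosing days, which addresses within-day meal effects. SAD fasting lipids are taken on Days -1 to 4. Alcohol abstinence starts 72 hours before admission, which weakens that source of drift after baseline.

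What remains is narrower but real. The Day -1 profile cannot show drift over 14 days of dosing. Whole blood for ABCA1/ABCG1 is scheduled only on Days 1 and 14, so it has no Day -1 reference. The SAD 4-hour markers have no reference day. Dose-response across cohorts helps, but does not replace a control. The pooling sentence in SAP 3.1 sits in a paragraph on safety and does not clearly settle PD or Part C.

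**Conclusion.** The concern stands in this limited form. Protocol 8.3.1.3 is wrong as written: it would drop every placebo subject (20 of 100, up to 30 of 150) and conflicts with 8.8 and 1.3.1. The SAP leaves the conflict open. For biomarkers outside the laboratory panel, the loss of control follows directly from the only definition given. For fasting lipids, placebo values will be displayed and only a placebo-adjusted estimate is missing.

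The counts assume that cohorts fill as planned. The precision and drift figures rest on assumed SDs and drifts. A half-width of 0.19 to 0.38 multiplies or divides a ratio by about 1.21 to 1.47: enough to describe an effect, not to prove one.

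A must-fix rating is not supported. The endpoints are exploratory, primary safety and PK are untouched, and placebo subjects are still randomised and sampled, so the comparison stays recoverable. This is a should-fix.

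**What to change.** 1. Redefine the PD Analysis Set, and add it to SAP Section 2, as all randomised subjects who received at least one dose of TLC-2716 or PTM from Day 1 on and have the baseline and on-study values needed for the parameter. The Day 1 condition matters because every MAD subject takes PTM on Day -1.
2. State that placebo is pooled across cohorts, separately for SAD and MAD. Pooling by part would mix the two in Part C. Say also how placebo from any fasted Part C cohort is handled for post-meal markers.
3. In SAP Sections 6 and 9, report for both SAD and MAD a descriptive difference from pooled placebo in change from baseline, with 95% CI, for each dose. For SAD this means the PD markers in Section 9, since Section 6 covers MAD only. Baseline-adjusted ANCOVA on the log scale is one suitable method; a simple difference in mean log change would also serve.

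The cost is wording in the protocol and SAP plus one simple analysis. No new data are needed, because placebo subjects follow the same PD schedule.

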## 8.4. Data Handling Conventions

For summary statistics, PK concentration values below the limit of quantitation (BLQ) will be imputed as zero at pre-dose and one-half of the lower limit of quantitation (LLOQ) for post-dose time points.

Laboratory data that are continuous in nature but are less than the LLOQ or above the upper limit of quantitation (ULOQ) will be imputed to the value of the lower or upper limit minus or plus one significant digit, respectively (e.g., if the result of a continuous laboratory test is < 20, a value of 19 will be assigned; if the result of a continuous laboratory test is < 20.0, a value of 19.9 will be assigned).

Missing data can have an impact upon the interpretation of the trial data. As this study is of short duration, it is anticipated that missing data will be minimal. In general, values for missing data will not be imputed. However, a missing pretreatment laboratory result would be treated as normal (i.e., no toxicity grade) for the laboratory abnormality summary.

## 8.5. Demographic Data and Baseline Characteristics

Demographic and baseline measurements will be summarized, and descriptive statistics will be provided.

## 8.6. Safety Analysis

All safety data collected on or after the date that study drug was first administered up to the date of last dose of study drug plus 14 days will be summarized by treatment group (according to the study drug received) or treatment sequence using the Safety Analysis Set. As appropriate, placebo-treated subjects will be pooled across Parts A, B, and C of the study.

### 8.6.1. Extent of Exposure

A subject's extent of exposure to study drug data will be generated from the study drug administration page in the eCRF. Exposure data will be listed.

### 8.6.2. Adverse Events

Clinical and laboratory AEs will be coded using the Medical Dictionary for Regulatory Activities (MedDRA). System Organ Class (SOC), High-Level Group Term, High-Level Term, Preferred Term (PT), and Lower-Level Term will be attached to the clinical database.

Adverse event data will be listed by subject. Treatment-emergent AEs (TEAE), serious TEAE, and TEAE leading to discontinuation of treatment (as applicable) will be summarized by treatment, relationship to study drug, severity, as well as SOC, and PT using the current version of the MedDRA.

### **8.6.3. Laboratory Evaluations**

Listings of individual subject laboratory results will be provided. Selected laboratory data will be summarized by cohort at scheduled visits and for the corresponding change from Baseline (Day 1 pre-dose for SAD cohorts; Day -1 for MAD cohorts). The incidence of treatment-emergent, graded laboratory abnormalities will be summarized by cohort and treatment.

### **8.6.4. Other Safety Evaluations**

Vital signs and ECG data will be summarized by treatment sequence.

### **8.7. Pharmacokinetic Analysis**

Plasma concentrations and PK parameters (e.g.,  $AUC_{last}$ ,  $AUC_{inf}$  [single-dose],  $\%AUC_{exp}$  [single dose],  $CL/F$  [single dose],  $AUC_{tau}$  [multiple-dose],  $C_{tau}$  [multiple-dose],  $CL_{ss}/F$  [multiple dose], and  $V_z/F$ ,  $C_{max}$ ,  $T_{max}$ ,  $C_{last}$ ,  $T_{last}$ ,  $\lambda_z$ ,  $CL/F$ , and  $t_{1/2}$ , if applicable) will be listed and summarized for TLC-2716 (and its metabolites, as applicable) using descriptive statistics by treatment for each cohort.

Dose proportionality will be assessed by comparing PK parameters of TLC-2716 across evaluated dose levels. A power model will be fitted using all doses across cohorts to evaluate the dose proportionality based on  $AUC_{last}$ ,  $AUC_{inf}$  (single-dose),  $AUC_{tau}$  (multiple-dose),  $C_{tau}$  (multiple-dose), and  $C_{max}$ . The population mean slope will be estimated with a 90% confidence interval. An alternate evaluation of dose proportionality may be conducted using analysis of variance (ANOVA) on dose normalized, natural log-transformed AUC,  $C_{tau}$  (multiple-dose), and  $C_{max}$ . Dose proportionality analyses will be conducted separately for the single- and multiple-dose cohorts.

Additional analyses such as accumulation ratio and time to steady state may be conducted as appropriate. If fasted cohorts are conducted in Part C, an evaluation of the effect of fasting status on TLC-2716 PK may be conducted.

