### 6.3. Check-In Assessments

Following confirmation of study eligibility at Admission, eligible subjects will be randomized to receive TLC-2716 or PTM starting on Day 1 and assigned a subject number and study drug administration time. Note, for MAD cohorts, regardless of randomization outcome, all subjects will receive PTM corresponding to the dose to be evaluated in the planned cohort on Day -1.

Study procedures and assessments are outlined in Table 5 (for SAD cohorts) and Table 6 (for MAD cohorts).

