#### **8.1.4. Pharmacokinetic Statistical Analyses**

##### **8.1.4.1. Dose Proportionality**

Dose-proportionality of plasma TLC-2716 and its metabolites, PK parameters,  $C_{\max}$ ,  $AUC_t$ ,  $AUC_{\text{tau}}$ , and  $AUC_{\text{inf}}$ , as applicable for Part A, Part B, and Part C (as applicable) over the dose range tested will be investigated. A power regression model will be fitted to describe the relationship between Y ( $C_{\max}$ ,  $AUC_{\text{tau}}$ ,  $AUC_{\text{last}}$ , and  $AUC_{\text{inf}}$ ) and X (dose) under fasting conditions. The model is defined as:

$$\ln(Y) = \beta_0 + \beta_1 \ln(X), \text{ where Y is PK parameter and X is dose}$$

The null hypothesis that will be tested is that the AUCs and  $C_{\max}$  values are dose-proportional, or slope  $\beta_1=1$  is within 90% CI of the slope.

An alternative evaluation of dose proportionality may be conducted using analysis of variance (ANOVA) on dose normalized, natural log-transformed AUC and  $C_{\max}$  of TLC-2716 and its metabolites. The model will include dose as a fixed effect. The two-sided 90% CI for the ratio of dose comparisons will be constructed.

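### The single-dose proportionality slope in protocol 8.7 leaves out Part B's Day 1 Cmax, and SAP 8.1.4.1 does not settle which cohorts, PK day or meal state enter the model.

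*Combined protocol and SAP*

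**What the plan says.** Protocol 8.7 sets out the power model: "A power model will be fitted using all doses across cohorts to evaluate the dose proportionality based on" AUC, Ctau and Cmax. It adds "The population mean slope will be estimated with a 90% confidence interval" and then the separation rule: "Dose proportionality analyses will be conducted separately for the single- and multiple-dose cohorts". Single-dose cohorts here means Part A plus any single-dose cohorts opened in Part C.

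SAP 8.1.4.1 describes the analysis differently. Proportionality, "as applicable for Part A, Part B, and Part C (as applicable) over the dose range tested will be investigated". The separation rule is not repeated, and no PK day is named for Part B. The regressor is given as X, "dose) under fasting conditions". The slope is read as consistent with proportionality if the value 1 "is within 90% CI of the slope".

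On the design, Tables 2 and 3 of the protocol list the same five doses for Parts A and B, all fed, and each cohort has 8 active subjects. Section 6.3 says that in multiple-dose cohorts "all subjects will receive PTM corresponding to the dose to be evaluated in the planned cohort on Day -1", so Day 1 is the first active dose. Section 6.5.1 gives the same Day 1 sampling times to 12 hours in both parts. Part A continues to 72 hours. Part B Day 1 stops at 12 hours in the protocol, while SAP 8.1.2 adds a 24-hour sample.

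**The concern.** Single-dose PK is a primary objective and Cmax is among the primary endpoints, yet the first-dose slope is estimated without half of the planned first-dose Cmax data from Parts A and B. No precision target is set (protocol 8.10), so the precision of the slope depends entirely on which collected data are used.

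The SAP's reading rule gives this a direction. Because proportionality is retained whenever 1 lies inside the interval, a wider interval makes that conclusion easier to reach, and a real departure is more likely to pass unnoticed.

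The SAP wording adds a second problem. Read literally, a model restricted to fasting conditions admits no Part A or Part B data at all. With the PK day also unstated, two analysts could fit different models from the same text.

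**Working it through.** The plan gives no precision figure for the slope, so there is none to reproduce.

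**Inputs**
- Doses 0.5, 2, 6, 12 and 20 mg in both parts (protocol Tables 2 and 3).
- 8 active subjects per cohort, so 5 × 8 = 40 per part and 80 in the two parts. The share outside the single-dose slope is 40/80 = 50%.
- Between-subject CV of Cmax: **not given; assumed 30% to 60%**.

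**Spread of ln(dose).** The values are −0.693, 0.693, 1.792, 2.485 and 2.996, with mean 1.454. The squared deviations are 4.612 + 0.580 + 0.114 + 1.062 + 2.375, so S = 8.743.

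**Standard error of the slope**, with n subjects per dose and σ = √ln(1 + CV²): SE = σ/√(nS).
- Part A: σ/√(8 × 8.743) = σ/8.36, with 40 − 2 = 38 df and t(0.95) = 1.686.
- Parts A and B with a part term: σ/√(16 × 8.743) = σ/11.83, with 80 − 3 = 77 df and t(0.95) = 1.665. Both parts have the same doses and numbers, so the part term costs one degree of freedom and nothing else.

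**Ratio of half-widths:** (1.665/11.83)/(1.686/8.36) = 0.698. The interval is about 30% narrower whatever the CV.

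| Assumed CV | σ | 90% half-width, Part A | 90% half-width, A + B Day 1 |
|---|---|---|---|
| 30% | 0.294 | 0.059 | 0.041 |
| 40% | 0.385 | 0.078 | 0.054 |
| 60% | 0.555 | 0.112 | 0.078 |

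Over the 40-fold range (20/0.5), the half-width at CV 40% becomes a factor of 40^0.0777 = 1.33 with Part A and 40^0.0542 = 1.22 with both parts.

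**Effect on the SAP's rule.** Take a true slope of 1.10, which is a 40^0.10 = 1.45-fold deviation over the range. From the noncentral t distribution with noncentrality 0.10/SE, the chance that the 90% interval excludes 1 rises from 69% to 92% at CV 40%, and from 54% to 80% at CV 50%.

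**Which parameters gain.** Cmax is comparable across parts. A fixed-window AUC0-12 would be too, but it is not among the planned parameters. AUClast and AUCinf rest on sampling to 72 hours in Part A and to 12 hours (protocol) or 24 hours (SAP) on Part B Day 1, so they gain nothing.

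**How well a common slope can be checked.** The difference between the two part-specific slopes has SE = σ√(2/(8S)) = σ/5.91. At CV 40% that is 0.385/5.91 = 0.065, so its 90% half-width is about 1.67 × 0.065 = 0.11. The check would reveal a gross difference between parts, not a small one.

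**The case against.** Separate analysis is prespecified and unbiased. Dose escalation rests on review of the data, not on this interval, and Part A alone already gives a usable slope. Pooling also assumes a common slope and residual variance, while Part B seeks at least 3 subjects per cohort with raised triglycerides or LDL-C and Part A does not. A part term shifts only the intercept. All of this stands. It is why the pooled model belongs beside the planned analyses, with a part-by-ln(dose) check, and not in their place.

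A reader might infer more than the documents support:
- *That the single-dose slope uses Part A alone.* Protocol 8.7 speaks of single-dose cohorts, so single-dose Part C cohorts would enter. The 50% share is for Parts A and B only. If all five Part C cohorts were run, the share of first-dose active subjects left out would be 5/15 = 33% if all were single-dose and 10/15 = 67% if all were multiple-dose.
- *That both documents exclude Part B Day 1.* Only the protocol's split does so. The SAP is silent on pooling and PK day, which is a gap, not an exclusion.
- *That the Part B Day 1 data are discarded.* They feed the accumulation ratios and the Day 14/Day 1 comparison (SAP 8.1.3 and 8.1.6), though these do not inform the first-dose slope.
- *That every exposure slope would tighten by 30%.* The gain is for Cmax, and for AUC0-12 if that is added.

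**Conclusion.** The point holds as a matter of efficiency and specification. Under protocol 8.7, first-dose Cmax from 40 of 80 planned active subjects in Parts A and B stays outside the single-dose slope, and using it would narrow the 90% interval by about 30%. The percentage does not depend on the CV. The absolute half-widths do, and the CVs are assumptions. The figures also assume that all ten cohorts of Parts A and B are run at full size and at the planned doses (each part has up to five cohorts, and doses may be modified), that slope and residual variance are common to the parts, and that no single-dose Part C cohort enters the comparison.

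The conflict between the SAP's fasting condition and fed dosing in Parts A and B comes first, because until it is resolved the cohorts entering the model are undefined. The planned separate analyses are not invalid.

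**What to change.** In protocol 8.7 and SAP 8.1.4.1:
1. Reconcile the SAP's fasting condition with the fed dosing of Parts A and B.
2. For each proportionality model, state the cohorts, the PK day and the parameters, including how Part C cohorts enter.
3. Keep the separate analyses and add a first-dose power model for Day 1 Cmax across the fed Part A and Part B cohorts: one record per subject, part as a fixed effect, and a part-by-ln(dose) term reported as a check on the common slope.
4. Optionally, fit the same model to AUC0-12, with its own rule for values below quantitation. SAP 8.1.1 sets terminal BLQ values to missing, and nonclinical plasma levels were undetectable 2 to 4 hours after dosing (protocol 1.2.3), so a fixed window cannot rely on the existing rule.

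The cost is wording and one extra model. Day 1 Cmax in the multiple-dose cohorts is already derived for the accumulation ratio, and no further subject or sample is needed. AUC0-12 would be a new derivation. The drawback is the common slope and variance assumption, which the check in step 3 tests only coarsely.
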